## Purpose

This document describes a pre-analysis plan for a study examining the child health consequences of antenatal corticosteroid administration in a population-based cohort of linked administrative and clinical records from British Columbia, Canada. We use a regression discontinuity design that exploits the pronounced change in antenatal corticosteroid administration practices based on a clinical practice guideline that recommended administration up to 33 weeks, 6 days of gestation (33+6 weeks), but not at or beyond 34+0 weeks. This pre-analysis plan was written after the individual datasets had been received and some descriptive statistics calculated for key variables, but prior to the linkage of the datasets or analyses linking exposure with longer-term child health outcomes.

## Introduction

Randomized trials have consistently shown that administering antenatal corticosteroids to pregnant women at risk of preterm labour reduces neonatal mortality and respiratory morbidity. As a result, Canadian and international practice guidelines unequivocally advise that all eligible women at 26 to 34 weeks' gestation at risk of an imminent preterm delivery (due to spontaneous onset of labour, preterm premature rupture of membranes, or pregnancy complication indicating an early delivery) should be given antenatal steroids. Antenatal steroids are a *WHO Priority Life-Saving Medicine*, and administration rates are audited as an indicator of perinatal care quality in multiple jurisdictions including Canada.

However, we still lack high quality evidence on the longer-term safety of antenatal corticosteroids. Select studies have signalled that antenatal steroids may have harmful consequences for child neurodevelopment, and obstetrical leaders are beginning to advocate for more restricted use until long-term safety has been convincingly demonstrated. However, generating rigorous evidence on the effects of antenatal steroids for child neurodevelopment is challenging. Follow-up studies of randomized trials were hampered by low follow-up rates and small sample sizes, and observational studies are highly susceptible to confounding. Without high-quality safety evidence, the unproven potential for harm may be causing a treatment with proven neonatal benefits to be withheld unnecessarily.

When randomization is infeasible, regression discontinuity (RD) studies can provide credible causal effect estimates. The design exploits differences in care between individuals immediately on either side of a clinical cut-point as a quasi-randomization tool. With antenatal corticosteroids guidelines recommend administration of corticosteroids up to 33+ 6 weeks' gestation – but not one day later, at 34 weeks+ 0 days, so infants born as little as hours apart have substantially different chances of receiving the treatment. We propose to use this novel design to generate rigorous evidence on the longer-term safety of antenatal steroids. We also propose to examine if antenatal corticosteroid administration's protective effect on respiratory morbidity extends into early childhood.

## Objectives

To determine if antenatal corticosteroid administration:

- 1) decrease kindergarten child development scores (primary outcome)
- 2) increase risks of adverse neurodevelopmental outcomes such cerebral palsy or attention deficit hyperactivity disorder (ADHD) (secondary outcomes), and
- 3) decrease the risk of lower respiratory tract infection hospital admission under the age of two or childhood asthma (secondary outcomes).

## Overview of research plan

We will estimate the effect of antenatal corticosteroid use on child neurodevelopmental outcomes using a novel quasi-experimental design that exploits the clinical cut-off of antenatal corticosteroids administration at 34 weeks. We will link abstracted obstetrical and neonatal chart records from approximately 16,000 preterm births delivered from 2000 to 2013 contained in the British Columbia (BC) Perinatal Data Registry with longer-term child health information contained in BC population-based administrative databases and kindergarten testing data. We will isolate the difference in test scores and adverse child health outcomes occurring at 34 weeks using a regression discontinuity design, while accounting for the general decrease in adverse outcomes associated with advancing gestational age. The study was approved by the Research Ethics Board of the BC Children's & Women's Hospital/University of British Columbia (H18-00620).

## Study population

Our study population will be drawn from all singleton deliveries in British Columbia, Canada admitted

for the delivery admission between 31+0 and 36+6 weeks, inclusive, from April 1, 2000 to March 31, 2013. Late pregnancy terminations and pregnancies with no ultrasound-confirmed, day-specific estimate of gestational age will be excluded.

## **Data**

Our study cohort will be created through a linkage of British Columbia's comprehensive population-based databases of detailed obstetrical medical records, medication prescriptions, physician billing, hospital discharge records, vital statistics, and kindergarten child development assessments. The linkage will be performed by PopData BC, a multi-university organization that facilitates the use of the province's databases for research purposes. Maternal and infant personal health numbers and dates of birth will be used as unique identifiers. The linked data are accessed in an anonymized format on a secure server to ensure data confidentiality and security. Follow-up data up to March 31, 2018 will be included, ensuring a minimum of 5 years follow-up for all children.

**BC Perinatal Data Registry:** The BC Perinatal Data Registry contains abstracted obstetrical and neonatal medical records for >99% of deliveries in the province since April 1, 2000. Data quality are maintained through the use of provincially-standardized medical record forms, standardized training of abstractors (certified following a 2-year training program), and regular data checks for plausibility and missing values. Validation studies have established the accuracy and completeness of the database.

**Early childhood development data:** British Columbia has been conducting standardized assessments of child development at kindergarten age since 2001 using the Early Development Instrument, a questionnaire used across Canada and internationally. Data are collected in 3-year waves, so are only available for approximately one-third of children in the province a given year.

**Hospital Discharge Abstract Database:** The BC Hospital Discharge Abstract database contains International Classification of Disease (ICD) codes summarizing the diagnoses and procedures for all discharges, transfers and deaths of inpatients in acute care hospitals in British Columbia. We will only use the first 16 diagnostic coding spots, to ensure that the number of diagnostic coding spots is consistent throughout the study period (a greater number of spots are available in more recent years).

**Physician billing records:** These records contain data on medically required services provided by fee-for-service practitioners to individuals covered by BC's universal insurance program. These are collected in ICD-9 format. These codes have been validated at the population level.

**BC Vital Statistics Deaths:** The BC Vital statistics Agency records all deaths registered in BC.

**Pharmanet:** The BC PharmaNet database documents all prescription medications dispensed by community pharmacies in the province, as well as all prescriptions dispensed from hospital outpatient pharmacies for patient use at home. Data are available from Jan 1, 1996 onwards.

**Consolidation file:** The Consolidation file is a central demographic file containing information such as location of residence, enabling linkage of an individual's postal code of residence with postal code level census information such as median neighbourhood income quintile.

## **Exposure measurements**

**Gestational age** in days will be calculated using the gestational age algorithm used clinically during the study period. The estimate of gestational age will be based on the last menstrual period if this estimate is similar to the estimate based on early ultrasound ( $\leq 5$  days if the ultrasound was performed  $< 14$  weeks;  $\leq 10$  days if the ultrasound was performed  $< 20$  weeks). If the gestational age estimate based on last menstrual period disagrees with early ultrasound, or no last menstrual period estimate is available, the ultrasound estimate will be used. Day-specific estimates of ultrasound-based gestational age are available in the BC Perinatal Data Registry as of April 1, 2008. Prior to this period, we will calculate day-specific gestational age based on the date of the last menstrual period among women

whose ultrasound-based estimate of gestational age (in weeks) is the same or within 1 week of their estimate based on last menstrual period (in weeks). We will use gestational age in days at the time of maternal admission for the delivery as our unit of analysis, which better approximates timing of antenatal corticosteroid administration compared with gestational age at delivery. We will conduct sensitivity analyses to explore the potential for bias due to exclusion of women with missing day-specific gestational age estimates.

Antenatal corticosteroid administration is available in the BC Perinatal Data Registry as a binary variable indicating the administration of corticosteroids during the delivery admission for the purpose of fetal lung maturation. This can be any type of corticosteroid (e.g., betamethasone or dexamethasone) and does not reflect dosing information. This variable is known to underestimate the true administration rates, as administration during an antenatal admission shortly prior to delivery is not captured (i.e., a patient is admitted, receives antenatal corticosteroids, but is discharged without delivering). We will obtain this variable to confirm the change in the probability of receiving antenatal corticosteroids according to gestational age, but are using the gestational age discontinuity, not the provision of steroids *per se*, as our primary exposure.

### Child health outcomes

We will examine adverse outcomes from different points along the spectrum of potential neurodevelopmental consequence, from more subtle differences in lower school development scores to serious adverse neurodevelopmental outcomes such as cerebral palsy. We will also determine if antenatal corticosteroid administration is protective against childhood respiratory conditions.

Our **primary outcome** will be the standardized domain scores of the Early Development Instrument (EDI). The Early Development Instrument was developed by researchers at McMaster University to measure children's development in kindergarten. The EDI provides a holistic assessment of children's development through 104 questions across five domains: physical health and well-being, social competence, emotional maturity, language and cognitive development, and communication skills. The assessments are completed by kindergarten teachers in February for each child in their class, after the teachers have had several months of interaction with the children.

The EDI has been shown to be a reliable and psychometrically-sound tool to measure population-level child development, and is a good predictor of adult health, education and social outcomes. It is used by governments in multiple Canadian provinces (such as Ontario, Manitoba, and British Columbia) and internationally (Australia, Hong Kong) to assess kindergarten readiness and child development. Its widespread use will facilitate the interpretation and comparison of scores from our research.

Each of the five EDI domains are relevant to the detection of adverse neurodevelopmental outcomes. For example, in the physical health domain, questions such as "Can the child manipulate objects?" will capture concerns about fine motor skills and coordination, which are more subtle outcomes on the spectrum to cerebral palsy. Likewise, in the emotional maturity domain, questions such as "Is the child distractable, has trouble sticking to any activity?" assesses characteristics of ADHD. The scores from each domain are standardized into mean scores, and will be examined as continuous variables. We will consider a difference in the total EDI of 5 or greater to be clinically significant. This would reflect a child who scoring 1 point out of 10 lower on each of the 5 subscale domains, and corresponds approximately to the difference between the score of a child on the 50th percentile (41/50) and that of a child on the 25th percentile score (35/50). We will also examine a composite outcome of 'developmentally vulnerable', which is defined as a score <10th percentile on at least two domains (secondary outcome), and an indication of whether the child was identified as having special needs.

Other **secondary neurodevelopmental outcomes** will be cerebral palsy and ADHD, based on previously-published definitions from BC administrative data. Cerebral palsy will be identified using

International Classification of Disease (ICD) codes from hospitalization and physician billing records. ADHD will be identified using prescription records for methylphenidate (Ritalin) and other ADHD medications, based on pediatric ADHD prescribing patterns in Canada described in recent national Canadian Primary Care Sentinel Surveillance Network data. Our **secondary respiratory outcomes** will be a diagnosis of asthma (based on two or more physician billing records or a hospitalization for asthma) and any hospital admission for lower respiratory tract infection during the first two years of life. See Table 1 for detailed outcome definitions.

For all analyses, infant or child deaths (identified based on vital statistics records) will be assigned the lowest observed score (for EDI scores) or occurrence of the adverse outcome. This will be done to prevent selection bias introduced from differential losses to follow up according to antenatal corticosteroid administration status (i.e., having fewer cases of cerebral palsy in the untreated group because those infants who didn't receive treatment didn't survive infancy to develop the condition).

| Table 1. Study outcome definitions                                               |                                                         |                                                                                                                                                                                                                                                                                           |
|-----------------------------------------------------------------------------------------|---------------------------------------------------------|-------------------------------------------------------------------------------------------------------------------------------------------------------------------------------------------------------------------------------------------------------------------------------------------|
| Outcome                                                                          | Data source                                      | Definition                                                                                                                                                                                                                                                                         |
| Kindergarten age child development scores                                               | Early Development Instrument                            | Mean domains scores for each of:
1. Language and cognitive development
2. Physical well-being
3. Social competence
4. Emotional maturity
5. Communication and general knowledge                                                                                            |
| Developmentally vulnerable                                                              | Early Development Instrument                            | Score <10 th percentile for two or more domains                                                                                                                                                                                                                   |
| Special needs                                                                           | Early Development Instrument                            | Flag indicating the child has special needs                                                                                                                                                                                                                                               |
| Cerebral palsy                                                                          | Hospital discharge records and physician billing claims | ICD-9 code 343 or ICD-10 code G80, with two confirmatory diagnoses if initial diagnosis was prior to age 3                                                                                                                                                                   |
| ADHD                                                                                    | PharmaNet                                               | ≥ 1 prescription of methylphenidate, amphetamine and its derivatives, or atomoxetine (ATC codes N06B)                                                                                                                                                                  |
| Childhood asthma                                                                        | Hospital discharge records and physician billing claims | ICD-9 code 493 or ICD-10 code J45, with two confirmatory diagnoses if based on physician billing, or diagnosis in the primary diagnosis position (most responsible) for hospital admissions.                                                                                              |
| Hospital admission for lower respiratory tract infection in the first two years of life | Hospital discharge records                              | Hospitalization of a child aged 2 or less with any of the following ICD-9 or ICD-10 codes:
466.0 or J20 Acute bronchitis
466.1 or J21 Acute bronchiolitis
480–486 or J12-J18 Pneumonia
487 or J10- J11 Influenza, excluding cases due to certain identified influenza viruses |

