### Statistical analysis

We will isolate the effects of antenatal corticosteroid administration practices using a regression discontinuity design. This design exploits the fact that an infant's probability of receiving antenatal corticosteroids changes significantly based on whether its mother presented to hospital before or after

the 34 week gestational age cut-off. The design assumes that infants immediately below the 34-week threshold are exchangeable with those immediately above the threshold except for the probability of receiving antenatal steroids, mimicking random treatment assignment. In the absence of any treatment effect, outcome rates should be smooth across the 34-week threshold, therefore any estimated change in the outcome at 34 weeks can be assumed to be due to antenatal corticosteroid treatment.

We will implement the design using a multivariable quantile regression model estimating the 50th percentile (for our primary outcome of EDI scores), multivariable log-binomial models (for binary outcomes such as developmentally vulnerable, special needs, and lower respiratory tract infection hospitalization in the first two years of life), and pooled logistic regression models (for binary outcomes where children born in different study years have follow-up time such as ADHD and asthma). In the event that our log-binomial models fail to converge, we will use logistic regression and convert odds ratios to risk ratios using postestimation commands.

Our primary model will include delivery admissions between 31+0 and 36+6 weeks. We will weight observations according to their proximity to the cut-off of 34+0 using a triangular kernel, such that observations closest to the discontinuity are assigned greater weight and those furthest from the discontinuity are given less weight. This weighting is particularly important in this cohort as the probability of birth increases with advancing gestational age, so the largest number of observations will occur furthest from the discontinuity (i.e., at 36+6 weeks).

We will use standard regression discontinuity methods to estimate the size of the discontinuity in child health outcomes due to crossing the threshold at 34+0 weeks (Lee & Lemieux 2010). We will estimate the following regression models for individuals in our sample using a 3-week bandwidth around the gestational age threshold:

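### As written, the EDI analyses take in all deaths but only about one-third of survivors, so deaths are over-represented about threefold and the two binary EDI outcomes lean towards apparent steroid benefit

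*Protocol*

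**What the plan says.** Three statements in the Protocol bear on this.

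- **Death rule (Child health outcomes).** "For all analyses, infant or child deaths (identified based on vital statistics records) will be assigned the lowest observed score (for EDI scores"), with binary outcomes given "or occurrence of the adverse outcome". The stated aim is to avoid selection bias when deaths differ by treatment. The rule has no time limit and is not restricted to children whom an EDI collection would have reached.
- **Source of deaths (Data).** "The BC Vital statistics Agency records all deaths registered in BC".
- **EDI coverage (Data).** "Data are collected in 3-year waves, so are only available for approximately one-third of children in the province a given year".

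Three EDI-based results are planned: the domain scores (primary), developmentally vulnerable, and special needs. For the primary outcome, under Statistical analysis: "We will implement the design using a multivariable quantile regression model estimating the" 50th percentile. The two binary outcomes use log-binomial models, which give risk ratios. The sensitivity analyses listed include neither a survivors-only EDI analysis nor any matching or weighting of deaths to EDI coverage.

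**The concern.** A child passes through kindergarten once, so if about one-third of children are assessed in a given year, about one-third of survivors will have an EDI. Deaths need no EDI: the rule supplies their value. The EDI analysis set then holds essentially every registered death and about a third of the survivors, so entry to it depends on having died. The rule was adopted to prevent selection bias, and applied this way it introduces some.

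The direction matters for a safety study. The Introduction says that giving steroids "reduces neonatal mortality and respiratory morbidity". If so, the surplus deaths fall more on the less-treated side, at 34+0 weeks and later. That raises the apparent event risk there and makes steroids look more favourable on the binary EDI outcomes. Objectives 1 and 2 are to detect harm, so the error runs towards false reassurance.

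**Working it through.** The Protocol gives no mortality, sample-size or power figure for the EDI analyses, so there is no stated figure to reproduce.

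**Inputs**

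- From the Protocol: EDI coverage f of about 1/3; deaths captured in full; a cohort of "approximately 16,000 preterm births delivered from 2000 to 2013"; total EDI of 41/50 at the 50th percentile and 35/50 at the 25th; a 5-point difference in total EDI taken as clinically significant.
- Assumed, because the documents give none: mortality d, and the event risk p in survivors.

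**Step 1: death share in the EDI set.** s = d / (d + (1 − d) × f).

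With d = 1.0% and f = 1/3: 0.010 / (0.010 + 0.330) = 2.94%, an over-count of 2.94 times. In counts, if all 16,000 births were in the set's catchment: 160 deaths stand beside 15,840 / 3 = 5,280 assessed survivors. Deaths sampled like survivors would number about 53, giving a share of 1.0%.

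The factor hardly depends on mortality: 2.99 at d = 0.25%, 2.97 at 0.5%, 2.88 at 2%, 2.83 at 3%. It does depend on coverage: at d = 1% it is 3.9 for f = 0.25 and 2.0 for f = 0.5.

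**Step 2: primary outcome (median).** With a share s placed at the bottom, the overall median is the (0.5 − s)/(1 − s) quantile of survivors. The Protocol's two percentiles imply a normal SD of 6 / 0.6745 = 8.9. Spurious advantage to the lower-mortality side, in total EDI points:

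| Mortality, less vs more treated | As written | Deaths matched |
|---|---|---|
| 0.5% vs 0.35% | 0.05 | 0.02 |
| 1.0% vs 0.7% | 0.10 | 0.03 |
| 2.0% vs 1.4% | 0.21 | 0.07 |
| 3.0% vs 2.0% | 0.35 | 0.12 |

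All are small against 5 points.

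**Step 3: binary EDI outcomes.** The analysed risk on each side is s + (1 − s) × p. Take the same p on both sides, so that the true risk ratio in survivors is 1.00, and mortality of 1.0% below the cut-off. As written, the death shares are 2.94% below, and 3.23%, 3.52% and 4.37% above for mortality of 1.1%, 1.2% and 1.5%.

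Worked line, 1.0% vs 1.5%, p = 5%:
- As written: below 0.0294 + 0.9706 × 0.05 = 7.79%; above 0.0437 + 0.9563 × 0.05 = 9.15%; RR 0.85.
- Matched: below 0.010 + 0.990 × 0.05 = 5.95%; above 0.015 + 0.985 × 0.05 = 6.43%; RR 0.93.

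| Mortality above cut-off | p = 5%, as written | p = 5%, matched | p = 15%, as written | p = 15%, matched |
|---|---|---|---|---|
| 1.1% | 0.966 | 0.984 | 0.986 | 0.995 |
| 1.2% | 0.935 | 0.969 | 0.973 | 0.989 |
| 1.5% | 0.852 | 0.926 | 0.935 | 0.974 |

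**Step 4: harm that would be hidden.** The survivor risk below the cut-off that would give an RR of exactly 1.00 is (risk above − s below) / (1 − s below). With 5% above, a rise to 5.3%, 5.6% or 6.4% would be hidden as written (mortality above of 1.1%, 1.2%, 1.5%). With matched deaths the figures are 5.1%, 5.2% and 5.5%.

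**The case against.** **The death rule is deliberate.** Counting death as a poor outcome has a stated reason and a cited precedent. That stands: the composite is not the error. Some pull towards benefit remains even with deaths correctly sampled (the matched columns), and that part belongs to the composite. Separate rows for death and for survivors would help a reader, but they are a reporting preference.

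**The primary outcome is a median.** This also stands. A reader might infer that the primary EDI result is compromised; the shifts above do not support that.

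**The mortality contrast is assumed, and the main estimate is intention-to-treat.** Imperfect compliance dilutes any jump in mortality at 34+0 weeks, so 1.0% vs 1.5% is the demanding end of the range. At 1.0% vs 1.1% the as-written and matched risk ratios differ by only about 0.02. The size of the bias is therefore uncertain; the threefold over-count that drives it is not, given one-third coverage.

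**Other outcomes.** A reader might extend the over-count to cerebral palsy, ADHD, asthma or lower respiratory tract infection admission. Those come from hospital, billing and prescription records, which do not depend on EDI collection, so the documents do not support that.

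**Late deaths.** Read literally, a death after kindergarten would overwrite a recorded EDI score, and a death at age 10 would count as a respiratory admission in the first two years. The stated purpose suggests this is not intended. It is a minor wording gap, but the text leaves it open.

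**Conclusion.** The point holds for the EDI analyses. Following the text puts essentially all registered deaths but about one-third of survivors into them, and inflates the death share 2.8 to 3.0 times for mortality between 0.25% and 3%. This rests on reading the Protocol's coverage statement as about one-third of survivors having an EDI; at 50% coverage the factor would be 2.0.

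The consequence is material only for special needs and developmentally vulnerable, and it favours steroids only if steroids lower mortality at the cut-off. With assumed mortality of 1.0% below and 1.1% to 1.5% above, the RR is 0.97 to 0.85 as written against 0.98 to 0.93 matched at 5% survivor risk, and 0.99 to 0.94 against 0.995 to 0.97 at 15%. The effect on the primary median is about 0.05 to 0.35 point over the mortality scenarios in Step 2. The missing time limit is a separate and smaller flaw.

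**What to change.** Amend the death rule in Child health outcomes in two respects.

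1. **Match deaths to EDI coverage.** In the EDI analyses, include a death only if that child's expected kindergarten year (and area, if coverage turns out to vary by area) was covered by EDI collection. Alternatively, keep all deaths at weight 1 and weight each assessed survivor by the inverse of the EDI capture probability estimated from the linked data. Either brings the death share back to the true mortality; in the illustration, 2.9% returns to 1.0%. The Protocol does not describe how coverage varies, so the matching variables should be named once the coverage pattern is known and before outcomes are analysed.
2. **Limit the rule in time.** Apply it only to deaths before the outcome's own assessment: before the EDI for EDI outcomes, and before the end of the two-year window for lower respiratory tract infection admission.

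The cost is a few lines of plan text, a little programming with data already due to be linked, and slightly larger variance. The plan was written before linkage, so making the change at that stage keeps it prespecified.

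### Every death enters the EDI analyses but only about one-third of survivors do, so death is over-weighted about threefold, which matters for the two binary EDI outcomes

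*Protocol*

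**What the plan says.** Three statements in the protocol meet here.

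- Child health outcomes, on deaths: "For all analyses, infant or child deaths (identified based on vital statistics records) will be assigned the lowest observed score (for EDI scores"), and for binary outcomes "or occurrence of the adverse outcome". Deaths come from vital statistics, which the Data section describes as covering all deaths registered in the province. The stated aim is to avoid selection bias from differential mortality, illustrated with cerebral palsy.
- Data, on the EDI: "Data are collected in 3-year waves, so are only available for approximately one-third of children in the province a given year".
- Statistical analysis: EDI scores are analysed with a "multivariable quantile regression model estimating the" 50th percentile, and the binary EDI outcomes with "multivariable log-binomial models (for binary outcomes such as developmentally vulnerable, special needs" and others).

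The cohort is "approximately 16,000 preterm births delivered from 2000 to 2013". No section limits the deaths to children who could have had an EDI, weights them, or imputes an EDI for unassessed survivors. None of the listed sensitivity analyses changes how deaths enter the EDI analyses.

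**The concern.** The rule suits an outcome that can be ascertained in every child, such as cerebral palsy. The EDI is observed in a subset. A child passes through kindergarten once, so a survivor has roughly a one-in-three chance of an EDI record, whereas a child who died is included with near certainty. About two-thirds of the included deaths are children who would have had no EDI had they lived.

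This is separate from whether death should count as the worst outcome. Even if it should, the mix of dead and surviving children is wrong, because inclusion now depends on vital status. A rule meant to remove a selection bias therefore brings in another.

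The direction matters because this is a safety question. The Introduction states that steroids lower neonatal mortality. If deaths are fewer just below 34+0 weeks, over-weighting them adds apparent benefit on that side and offsets developmental harm among survivors. The per-protocol estimate divides the same discontinuity by the jump in steroid administration, so it carries the error on an enlarged scale.

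**Working it through.** The protocol states no death rate, EDI count or power calculation, so there is no figure of its own to reproduce.

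**Inputs from the protocol:** coverage f = 1/3; cohort about 16,000; EDI 25th and 50th percentiles of 35 and 41 out of 50; clinical threshold of 5 total points.

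**Assumed inputs:** mortality m, survivor risks p, and a normal spread of total EDI with SD = (41 − 35)/0.6745 = 8.9.

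**Step 1. Share of deaths in the EDI sample.** m′ = m/(m + (1 − m)f).

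| True mortality | Deaths in 16,000 | Survivors with EDI | Share m′ |
|---|---|---|---|
| 0.5% | 80 | 5,307 | 1.49% |
| 1% | 160 | 5,280 | 2.94% |
| 2% | 320 | 5,227 | 5.77% |
| 3% | 480 | 5,173 | 8.49% |

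The odds are inflated by exactly 1/f = 3. At 1% mortality, coverage of 0.28 or 0.40 gives 3.48% or 2.46%.

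**Step 2. Share of events that are deaths, at 1% mortality.** This is m/(m + (1 − m)p), with m′ in place of m for the plan as written. For p = 5% (special needs) deaths are 38% of events instead of 17%. For p = 15% (vulnerable) they are 17% instead of 6%.

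**Step 3. Effect on a binary outcome.** Composite risk = m + (1 − m)p with deaths in proportion, and m′ + (1 − m′)p as written. Suppose survivor risk is 15% above and 16% below 34+0 weeks.

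| Mortality, above to below | In proportion | As written |
|---|---|---|
| 1.0% to 1.0% (no jump) | +0.99 | +0.97 |
| 0.5% to 0.425% | +0.93 | +0.80 |
| 1.0% to 0.85% | +0.86 | +0.61 |
| 1.0% to 0.7% | +0.74 | +0.24 |
| 2.0% to 1.7% | +0.73 | +0.24 |
| 2.0% to 1.5% | +0.56 | −0.23 |

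Entries are percentage points, below minus above. For the 1.0% to 0.7% row as written, m′ goes from 2.94% to 2.07% and the composite from 17.50% to 17.74%. With no jump the risk ratio moves from 1.062 to 1.055.

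The sign reverses once 3 × odds(m below) drops under the odds of the m′ that leaves the composite unchanged:

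- At 1% above: m′ = (0.1750 − 0.16)/0.84 = 1.79%, odds 0.01818, divided by 3 = 0.00606, so m = 0.60%.
- At 2% above: m′ = (0.19904 − 0.16)/0.84 = 4.65%, odds 0.04874, divided by 3 = 0.01625, so m = 1.60%.

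A rarer outcome is more sensitive. With survivor risk of 5% against 6% and mortality of 1% against 0.5%, the risk ratio is 1.09 in proportion and 0.95 as written.

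**Step 4. Effect on the primary median.** With deaths at the bottom, the median is the survivor quantile at (0.5 − m)/(1 − m). The shift due to mortality, in total EDI points:

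| Mortality, above to below | In proportion | As written | Excess |
|---|---|---|---|
| 1.0% to 0.7% | 0.03 | 0.10 | 0.07 |
| 2.0% to 1.5% | 0.06 | 0.17 | 0.12 |
| 2% to 1% | 0.12 | 0.35 | 0.23 |
| 3% to 1% | 0.23 | 0.70 | 0.47 |

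**The case against.** Four objections deserve an answer.

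**The primary outcome.** A reader might infer that the primary result is seriously distorted. The documents do not support that. The model targets the median, which a few percent of worst scores hardly move: Step 4 gives an excess of about 0.1 total points in the main scenarios and below 0.5 at the extreme. The protocol's own yardstick is "We will consider a difference in the total EDI of 5 or greater to be clinically significant". The primary outcome is the set of domain scores, so the shift in any one domain should be smaller still. This objection stands in full.

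**The sign reversal.** A reader might also infer that the plan will turn harm into apparent benefit. The protocol gives neither a mortality rate nor a mortality discontinuity at 34+0 weeks. The primary coefficient is an intention-to-treat jump under imperfect compliance, so a mortality jump would be the steroid effect diluted by the change in administration. Assuming a 30% mortality reduction in infants whose treatment changes and a 50-point jump in administration, mortality falls by 15%, for example from 1.0% to 0.85%. Step 3 then shows attenuation without reversal. This stands: reversal is an extreme case, and attenuation is the supportable claim.

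**The analysis set.** The protocol says what value a death receives but never lists who belongs to the EDI analysis set, and a separate analysis plan might do so. This carries little weight. The document calls itself the pre-analysis plan, and it states a rule with explicit scope over all analyses. An analyst who follows it obtains the wrong mix.

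**The remedy.** Selecting deaths by district and assessment wave would need a wave calendar by place. The protocol does not say that waves rotate by district, and it lists no such calendar among the linked data. This stands, so a coverage weight is the safer remedy.

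**Conclusion.** The concern holds for the two binary secondary EDI outcomes and should be fixed. The threefold inflation of the odds of death follows from the protocol's own statements; only its consequence depends on assumptions. If mortality does not jump at 34+0 weeks, the result is slight dilution. If mortality is lower below the threshold, developmental harm is attenuated, from +0.74 to +0.24 points in the 1.0% to 0.7% scenario. Reversal, for a one-point survivor harm from 15% to 16%, needs mortality to fall to under about 0.60% from 1%, or under about 1.60% from 2%. The mortality rates, survivor risks and normal spread are assumptions; coverage of one-third is the protocol's approximate figure.

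The primary median is little affected. Cerebral palsy, ADHD, asthma and lower respiratory infection admission are sought in the whole cohort and are not over-counted in this way.

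**What to change.** Add a sentence to the handling of deaths. In EDI-based analyses, each death's kernel weight is multiplied by the proportion of surviving cohort children of the same birth year (and region, if available) who have an EDI record, with that proportion re-estimated in each bootstrap resample. The share of deaths then becomes mf/(mf + (1 − m)f) = m, the true mortality.

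If the EDI wave calendar can be obtained, an alternative is to include only deaths of children who would have been due for an EDI. Keep all deaths at full weight for outcomes ascertained in the whole cohort. A survivor-only EDI analysis reported alongside would show readers how much of each estimate comes from mortality.

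The cost is one sentence and one derived weight from data already being linked. The downsides are that the weight is estimated, and that a deceased child's region, if used, must come from the last known residence. The protocol says it was written before linkage, so the change can be made without knowledge of results.
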